#### IM instruments

The constructs within the IM will be measured by the Treatment Motivation Scale for forensic patients (TMS-f) [38]. The TMS-f consists of eight subscales, one scale for the motivation to engage in treatment (MET) and six scales for variables that are summarized as Internal Determinants of MET: problem recognition, distress, perceived legal pressure, perceived costs of treatment, perceived suitability of treatment and outcome expectancy. An additional scale assesses the patients’ tendency to respond according to social desirability. The items within the scale of ‘perceived legal pressure’ were adapted to fit a more broadly defined concept of perceived External Pressure, in order to fit all patients in our research population.

The TMS-f has a patient version (85 items) and a clinician version (7 items), and both will be used in our study. The TMS-f has been found to be a reliable and valid operationalisation of the constructs in IM [38,53,54]. However, the TMS-f has only been used in a forensic psychiatric setting and it remains to be determined whether the scale is also applicable outside this setting. In the total patient population in which the scale was validated, it was found that 61% of the patients had axis-I disorders, while strong characteristics of personality disorders were prevalent in 78% of patients [53,55]. The composite reliability of the scale ranges between α = .83 and α = .91 [38].

#### Psychosocial functioning

Psychosocial functioning will be measured with the Dutch version of the Health of the Nations Outcome Scales (HoNOS) [56,57]. The HoNOS form is completed via a semi-structured interview with the patient. The HoNOS quantifies health and social problems during the previous two weeks and contains 12 items that refer to behavioural problems, impairment, symptoms, alcohol and drug abuse, and social (dis)functioning. Three HoNOS addendum items are also administered. These refer to manic symptoms, treatment motivation and compliance with medication. The items are rated from 0 (no problem) to 4 (very severe problem). The HoNOS has shown to be reliable and sensitive to change [57]. In order to obtain a more differentiated understanding of the psychotic symptoms, five items from the Brief Psychiatric Rating Scale [58] will be administered additionally to the HoNOS items in the interview with the patient. These include suspiciousness, unusual thought content, grandiosity, hallucinations and blunted affect. The BPRS has been used in various settings and has shown good psychometric properties [59].

#### Quality of life

The Manchester Short Assessment of Quality of Life (MANSA) [60] will be used to measure quality of life. The MANSA is a self-report questionnaire administered to the patient to measure how satisfied the patient is in the following life domains: living situation, social relationships, physical health, mental health, safety, financial situation, work situation and life as a whole. Each question is answered on a 7-point scale (1 = not satisfied, 7 = very satisfied) and a composite (mean) score is calculated. The psychometric properties are satisfactory [60], and the scale has also been validated in a population of patients with severe mental illness [61].

### Covariables

#### Socio- demographic factors of patients and clinicians

Socio-demographic data on gender, age, ethnicity, marital status, living situation, housing, distance from the treatment location, educational background, income, treatment history, treatment duration, no-shows in the treatment in the previous twelve months, legal status, medication use, and DSM-IV diagnosis will be collected at baseline from the patient’s medical record. In case of missing information in the medical record, the patient will be asked to provide the information. Information on clinician sex, age, years of clinical working experience, and treatment team was collected from clinicians.

#### Insight into illness

Impaired insight has been associated with reduced treatment engagement and increased symptoms, as well as higher rates of involuntary detention [62]. The Insight Scale [63] will be used to measure a patients’ insight into illness. This 8-item self-report scale produces a total score that ranges between 0 and 12. It was found to be a reliable, valid and easily applicable measure [63].

#### Executive functions

There is considerable evidence for cognitive dysfunctioning, especially impaired executive functioning, in patients with severe mental illness [64-66]. Executive dysfunctioning has been found to contribute to poor insight in psychosis and might be related to poor treatment engagement [66]. As a measure for executive functions, planning ability was chosen. Although the Wisconsin Card Sorting Test (WCST; [67]) is typically administered as a measure for executive functioning [66], the inclusion of this test to our study instruments would increase the burden to the patients such that we decided it was unsuitable for administration. Alternatively, planning ability will be measured with the Zoo Map test, a subtest of the Behavioural Assessment of Executive Functioning (BADS) [68,69]. The Zoo Map test asks the patient to draw a route on a map of a zoo and to visit specific sites in the zoo while applying specific rules (e.g. ‘you can use the dotted pathways as often as you want, but the white pathways only once’). There are two subtests within the Zoo Map test: the first is unstructured, forcing the patient to plan his route independently. This indicates the extent to which the patient is capable of spontaneous planning. The second condition is structured and indicates a specific order in which the patient should visit the specific sites. This indicates the ability of a patient to follow a concrete, externally demanded strategy. Theoretically, it is expected that patients who find it difficult to develop logical strategies on the Zoo map test also have more difficulties with following a (complex) treatment regimen. The time used for planning and execution of the task and the number of mistakes (breaking a rule) are scored, and a profile score ranging from 0 to 4 for each subtest is then derived. The BADS has shown adequate validity and test-retest stability [69,70].

#### Therapeutic alliance

The therapeutic relationship is measured with the Helping Alliance Questionnaire (HAQ). The Dutch version of the HAQ comprises 11 items that are rated on a 5-point scale (completely disagree, disagree, neither agree nor disagree, agree, completely agree) [71]. Both a patient and a clinician version have been developed (example items include “I feel the clinician understands me”; “I understand the patient”). The HAQ contains two scales: Cooperation (Cronbach’s α = 0.88) and Helpfulness (Cronbach’s α = 0.76) [71]. Modest associations have been found between the therapeutic alliance and client outcomes in community mental health for patients with severe mental illness [72,73]. However, it has been noted that most studies performed in these settings have been limited by a lack of power and standardized measures [72]. Possibly, the current study can improve on these limitations.

#### Experienced stigma

Stigma will be measured using the 12-item ‘perceived devaluation and discrimination’ subscale of the self-report Stigma-Scale [74]. This subscale refers to the perception of common opinions about psychiatric patients, such as ‘Most people stay friends with someone who has had a mental illness’ and ‘Most people look down on people who have been hospitalized for mental illness’. The items are scored on a scale from 1 (strongly disagree) to 4 (strongly agree). A higher total scale score means more perceived stigmatization. The scale had acceptable reliability (Cronbach’s alpha = .78) and construct validity was demonstrated in studies predicting associations between stigma (as measured with the subscale of ‘perceived devaluation and discrimination’) and self-esteem, employment, demoralization, quality of life and treatment seeking in patients with mental illness [75,76].

#### Personality characteristics

The temperament dimensions from the Temperament and Character Inventory (TCI) [77,78] will be used to measure personality characteristics, in order to explore the relationship between temperament and motivation to engage in treatment. The temperament dimensions from Cloninger’s theory called novelty seeking, harm avoidance, persistence and reward dependence [78,79] are used in this study. Convergent validity exists in the form of studies comparing the TCI scales with other similar scales of validated personality tests [78]. The internal consistencies (i.e. Cronbach’s alphas) of the novelty seeking, harm avoidance, persistence and reward dependence subscales varied between α =0.62 and α =0.90 in psychiatric patients recruited from community mental health care [78]. The temperament dimensions are measured by items that can be scored as true or false.

### Procedures and randomization

Figure 3 shows the study procedures. Eligible clinicians and patients will mainly be approached via specific treatment programs that provide FACT (for a description of FACT see the section on Treatment As Usual). Clinicians who are willing to cooperate in this study will be informed by the principal investigator regarding the goals and procedures of the study and receive an information brochure. Two weeks after having received the information brochure, clinicians will be contacted to ask for participation and to sign informed consent.

**Figure 3 F3:**
[figure not shown]
Flowchart of MotivaTe-IT procedures.

After having received informed consent from the clinicians, randomization will be performed at either clinician-level or team-level. Where clinicians work in FACT-teams, randomization will be performed at team-level so that a whole team (all clinicians working in this team) will be allocated to either the TAU condition or motivation feedback condition. As teams often work with a shared caseload between clinicians in the same team, this decision was made in order to prevent possible cross-over of the feedback-condition to the TAU condition within teams. Where clinicians work in an outpatient clinic on a one-to-one basis (individual case-management) then randomization will be performed at the clinician-level. The allocation ratio is 1:1 (i.e. therapist vs. therapist and team vs. team, respectively). Stratification for diagnosis in advance was considered unrealistic and impractical, as we would then have to achieve equal numbers of each patient diagnosis in each treatment condition, while our randomization is at team-level and clinician-level. Therefore, we chose to use multivariate modelling with diagnosis as a covariate (see section 2.9 ‘Statistical analyses’). Randomisation will be performed by assigning each randomization unit (e.g. a team or a clinician) a unique number, which is entered in a computerized randomization program (http://www.randomization.com) that randomizes each unit to a single treatment by using randomly permuted blocks. The randomization is single-blind, as both the principal investigator and clinicians need to know which condition the clinicians are in, in order for the clinicians to receive the necessary training for the intervention condition (or not). As a consequence, only patients will be blind to treatment allocation at baseline assessment, while clinicians are not. Due to the nature of the trial, follow-up assessment can not be blinded.

Subsequently, clinicians are asked to provide a list of their entire caseload to the principal investigator (PI). The PI will remove patients from this list who do not fulfil the inclusion criteria or fulfil the exclusion criteria and subsqequently, the PI will randomly select 10 eligible patients from this list to be asked for participation in the study. Clinicians will inform their selected patients about the objectives of the study, and provide a full explanation of all procedures for the study. If patients are willing to participate, an appointment is scheduled for the administration of the HoNOS.

At the beginning of the appointment, again all procedures of the research study are explained to the patient and signed informed consent will be obtained by the research assistant. Written information will also be provided to the patient, which explains the nature of the intervention and provides contact details of the research team. Following the informed consent procedure, baseline assessment will take place.

The HoNOS will be administered by the case-manager of the patient accompanied by an independent research assistant, who will assist in the interview and scoring of the HoNOS. This decision was made for several reasons. The first is that the case-managers have been trained to administer the HoNOS for Routine Outcome Monitoring, which is primarily used in clinical practice to guide treatment plans and evaluations and is now secondary used as an outcome in the current research study. Combining the two approaches ensures that Routine Outcome Monitoring procedures can be maintained (by the case-manager) while research requirements can be met (by the independent research assistant monitoring the administration and scoring of the HoNOS). Secondly, the response rate for the interviews is expected to be higher if the patient is approached by a familiar person (the case-manager). This might typically be the case for the more paranoid or anxious patients. Third, the presence of an independent research assistant who is also trained in the administration of the HoNOS likely ensures that the HoNOS is scored appropriately, to minimise a possible bias that might occur if the case-manager alone would do this. The self-report questionnaires will be administered by research assistants, only sometimes in the presence of the case-manager when the patient is seen at home to ensure the safety of the research assistant or to minimise feelings of anxiety with patients (who might feel intimidated by an unfamiliar person), but always ensuring the confidentiality and anonymity of the collected data.

Assessments of the HoNOS and self-report questionnaires will take place at baseline and follow-up at 12 months. Baseline assessment will take place after randomization to reduce the variation in the time between baseline assessment and the start of the intervention. Measuring baseline status close to the start of the intervention ensures that the information obtained at baseline assessment is still up to date at the start of the intervention. A limitation to this approach is that clinicians are aware of the treatment allocation, which may bias their responses. This possible information bias can not be eliminated since clinicians in the motivation feedback condition have to be trained in the relevant procedures before baseline assessment, since shortly after they will start employing the feedback intervention. Patients however, will not be informed about their treatment allocation at baseline assessment and are therefore blind to treatment allocation at the start of the study. In case patients drop-out from treatment or complete their treatment before these 12 months have passed, information regarding the reason for ending the treatment and total treatment duration will be obtained.

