## Background

Disengagement and non-completion of treatment pose a major problem for the successful treatment of patients with severe mental illness, since it is associated with several clinical and socio-economical problems such as recurrent psychiatric problems, rehospitalisation, and increased risk of suicide and episodes of violence [1-3]. Estimates of treatment disengagement vary across different psychiatric patient populations and depend on the definitions of disengagement and non-completion. For example, non-adherence to antipsychotic medication among patients with psychotic disorders was observed in over 50% of patients [4,5], while non-completion of personality disorder treatment is estimated at 37% [6]. Lehner et al. [3] found that among individuals in treatment for severe mental illness, appointment failures ranged from 50% to 73%, drop-out estimates ranged from 14% to 92% and medication failure estimates ranged from 5% to 71%.

Research into the determinants of treatment engagement and completion of treatment in severe mental illness has revealed numerous important factors, including patient-related factors (e.g. age, ethnicity, beliefs about treatment efficacy, income level, psychiatric history), illness-related factors (e.g. the type of disorder, symptom severity, comorbidity) and treatment-related factors (e.g. treatment setting, type of treatment, treatment efficacy, adverse treatment effects, therapeutic alliance) [2,7-9]. Although some of these factors are static and can not be influenced, others are more dynamic and may therefore be targeted in interventions to enhance treatment engagement. One dynamic factor that has long been recognized as an important determinant of treatment engagement is the patient’s motivation to make the efforts required by the treatment [9-12]. However, due to an abundance of conceptualizations of the global term ‘motivation’, it has proven difficult for both academics and clinicians to effectively work with the concept. As Drieschner et al. [12] point out, despite a large amount of publications regarding treatment motivation, the concept remains ill-defined and is therefore a continued source of confusion. Therefore, more insight into the associations between determinants of motivation, actual motivation to engage in treatment, treatment engagement and psychosocial functioning may contribute to the effectiveness of psychiatric interventions.

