### Sample size and power calculations

The RCT was designed to enroll an average of 6 patients for each of 56 participating clinicians. The sample size was calculated on the basis of our primary hypothesis, that the intervention group (motivation feedback) would be more effective than the control group (treatment as usual) in enhancing treatment engagement, as measured with the Service Engagement Scale (primary outcome) at 12 months after baseline assessment. The difference between the motivation feedback group and control group for the primary outcome is based on a power of 0.80 and an alpha of 0.05 (two-tailed). Earlier studies regarding differences between feedback and treatment as usual (control) conditions have shown effect sizes (standardized mean differences) ranging from 0.34 to 0.92 [16,17], but were based on treatment progress and not (solely) on treatment motivation. One RCT studying the effects of treatment adherence therapy in patients with psychotic disorders used the SES as outcome measure and found an effect size of 0.39 [80]. Therefore, we expect an effect size of approximately 0.40. Using an unpaired t-test statistic, this resulted in a minimum of 123 subjects per condition. However, as patients are clustered within clinicians, and clinicians are clustered in teams, the patient and clinician observations can not be considered as independent of each other. The sample size was therefore adjusted by the (variance inflation) factor f = 1 + (m – 1)ρ, to account for the variance that would have been achieved had there been no clustering. The cluster size (m) is 6 (patients per clinician) and the within-cluster correlation (ρ) was estimated from a previous study to be around 0.07 [21]. Thus, the computed sample size was inflated by 1.35 to be at least 166 subjects per condition (minimally 332 in total). The SES is rated by clinicians and so we expect minimal loss to follow-up on the primary outcome, but to be on the safe side we will aim for 350 patients as the total sample size.

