### Statistical analyses

The data of the RCT will be analyzed according to the intention-to-treat principle. Baseline comparability between the intervention group and control group in demographic and clinical variables will be evaluated with independent samples t-tests and chi-square tests. Furthermore, non-responders (i.e. eligible patients who chose not to participate in the study) will be compared to responders with respect to background demographic and clinical variables with independent samples t-tests and chi-square tests. Logistic regression analysis will be applied to test for differences between the motivation feedback and control group with respect to the primary and secondary outcomes that are dichotomous variables, while (multiple) linear regression analysis will be used in case of continuous outcome variables. For individual categorical outcome variables, the effectiveness will be determined by odds ratios, including p-values (two-tailed). The effectiveness of the variables combined will be determined by ROC-curves (for categorical outcomes) and the individual odds ratios, R2 and the individual regression coefficients (for continuous outcomes). The Hosmer and Lemeshow goodness-of-fit test will be used in case of logistic regression. In case of multiple regression analysis the classical regression diagnostics will be applied for normality, (non)linearity, heteroscedasticity, (influential) outliers and interaction. A subgroup analysis will be performed for patients with psychotic disorders for the effects of the intervention upon their antipsychotic medication adherence. The analyses will be performed both unadjusted and adjusted for baseline differences of the distributions between the two treatment groups. In analyzing a specific outcome variable, the baseline score of that variable will be used as covariate. The analysis will be extended using multilevel analyses that takes the nesting of measurements into account. A clustering of outcomes is likely since a single clinician may treat several patients, and clinicians are clustered into teams. Multilevel modelling will be performed to check for any clustering effects on the primary outcome. In the multilevel analyses we consider the two measurements as the first level and the patient as the second level. We will explore whether the different treatment locations (FACT teams) and institutions (MHC Breburg and MHC WNB) can be considered as random factors in the modeling. We will identify predictive factors in estimating the outcome and whether there are predictive factors dependent on the type of treatment condition (interaction between baseline variables and treatment effect). Furthermore, we will take into account to what extent patients were exposed to the intervention by analyzing the dose-effect relationship. We expect (as is the case in most empirical studies in a psychiatric setting) that missing data will occur. We expect that the data will be Missing At Random (MAR), which is allowed to be a function of the observed variables (both covariates and outcome variables). If the assumption of MAR is violated, the pattern mixture model approach will be applied. In case predictor variables are missing, the method of multiple imputations or the maximum likelihood estimation method will be applied.

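### The protocol does not secure the 12-month SES for patients who leave care, and its safeguard against engagement-dependent missing data waits on a condition that observed data cannot establish

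*Protocol article*

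**What the plan says.** The primary outcome is the SES, a 14-item scale completed by clinicians (Primary and secondary outcomes; Treatment engagement). Table 1 schedules it for therapists at baseline and 12 months.

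Four statements bear on patients who leave before 12 months:

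- **Procedures and randomization:** "In case patients drop-out from treatment or complete their treatment before these 12 months have passed, information regarding the reason for ending the treatment" will be obtained, together with total treatment duration. The SES is not mentioned in this rule.
- **Sample size and power calculations:** "The SES is rated by clinicians and so we expect minimal loss to follow-up on the primary outcome". No rate is given. The minimum is 332 patients and the target 350.
- **Statistical analyses:** the analysis is by intention to treat. Missing data are expected and assumed to be MAR. Then: "If the assumption of MAR is violated, the pattern mixture model approach will be applied".
- **Background:** in severe mental illness "drop-out estimates ranged from 14% to 92" per cent, and non-completion of personality disorder treatment is put at 37%.

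Treatment engagement also lists data from patient files: missed appointments, reasons for drop-out, and admissions. Missed appointments are a secondary outcome.

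**The concern.** In most trials, leaving treatment is a nuisance to the outcome. Here it is the far end of the outcome. The patients whose SES is hardest to obtain are those whose score would say most about the intervention.

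Three statements combine badly. The rule for leavers does not secure the primary outcome. The expectation of minimal loss rests only on who fills in the form, and Study population defines that clinician by having the most frequent contact with the patient, which is contact that ends when the patient leaves. The one analysis that could probe missingness depending on unobserved engagement is held back until MAR is found to be violated.

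If feedback keeps poorly engaged patients in care, they are rated low in the intervention arm. Similar control patients leave and may have no rating. The comparison among rated patients would then understate the effect, and nothing that is certain to be run would show it.

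**Working it through.** **1. The plan's own sample size.** The inputs in Sample size and power calculations are: "based on a power of 0.80 and an alpha of 0.05 (two-tailed"), an effect size of 0.40, and m = 6 with ρ = 0.07.

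- Unclustered n per arm = 2(1.960 + 0.842)²/0.40² = 98.1, so 99 (100 by the exact t-test). The plan states 123. That figure does not reproduce, but it errs on the safe side: 123 per arm gives about 88% power at 0.40.
- Design effect = 1 + (6 − 1) × 0.07 = 1.35. Then 123 × 1.35 = 166.05, or 332 in total. This step reproduces.
- Margin for loss = (350 − 332)/350 = 5.1%.

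**2. The margin against the cited drop-out.** The lowest cited rate, 14%, is 14/5.1 = 2.7 times the margin. Keeping 332 rated patients would need 332/0.86 = 387 enrolled at 14% loss and 332/0.63 = 527 at 37%.

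**3. Power if the SES were missing at a given rate.** Effective n per arm = 350(1 − loss)/(2 × 1.35). Normal-approximation power = Φ(0.40 × √(n/2) − 1.96).

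| Missing SES | Patients rated | Effective n per arm | Power (normal) | Power (t-test) |
|---|---|---|---|---|
| 0% | 350 | 129.6 | 0.896 | 0.894 |
| 14% | 301 | 111.5 | 0.848 | 0.845 |
| 23% | 269.5 | 99.8 | 0.807 | 0.803 |
| 37% | 220.5 | 81.7 | 0.724 | 0.719 |

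These figures apply one rate to both arms and hold the design effect at 1.35. If clusters shrink with loss, power is slightly higher (0.86 at 14%, 0.78 at 37%). Clustering by team is not included and would lower it.

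**4. Bias if missingness follows engagement (illustrative).** If leavers score k SD below those who stay, and leaving differs between arms by p_control − p_intervention, the comparison among stayers differs from the full comparison by k(p_control − p_intervention). With k = 0.5 to 1.0 and a 10-point difference, that is 0.05 to 0.10 SD against a planned 0.40.

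A simulation used 400,000 patients per arm, a true effect of 0.40, baseline-to-follow-up correlation 0.6, drop-out log-odds rising by 1 to 2 per SD of lower engagement, no SES for any leaver, and baseline-adjusted complete cases:

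| Control drop-out | Estimated effect, slope 1 to 2 |
|---|---|
| 14% | 0.38 to 0.35 |
| 25% | 0.37 to 0.33 |
| 37% | 0.36 to 0.31 |

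With a slope of 0.5, the estimates are 0.393 at 14% and 0.387 at 37%. The correlation, the slopes and the complete absence of ratings are assumptions, not figures from the protocol.

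**5. The trigger.** MAR says that, given what was observed, missingness does not depend on the unobserved SES. The values needed to test this are the missing ones, so the same observed data can fit a MAR model and a non-MAR model equally well. The condition can therefore be neither met nor ruled out from the data. The SES has only two occasions, so no interim SES score is available to inform the MAR analysis.

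**The case against.** A reader might infer that only reason and duration are recorded for leavers, and so that the engagement outcome is missing for the disengaged. The protocol does not support this. The rule for leavers does not say only. Table 1 schedules the SES at 12 months with no exception for leavers. A clinician can complete the scale without the patient attending, and nothing in the text says that availability or help seeking could not be rated low for someone who has gone. File data on missed appointments, drop-out and admissions are also collected. An SES for leavers is neither planned nor ruled out.

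A reader might also infer that the trial is underpowered or that its intention-to-treat claim fails. Neither follows. The cited rates describe leaving treatment in other populations, not missing clinician ratings, and the Background itself says that they vary with population and definition. Because 123 is conservative, 350 patients keep 80% power up to about 23% loss. The simulated bias is towards the null, is small for a weak dependence (slope 0.5), and holds only under the assumptions listed.

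Finally, an article may leave to the full protocol who rates a leaver and when. That is fair for the detail. It does not cover what the article does state: a rule for leavers that passes over the primary outcome, a claim of minimal loss with no rate, and a trigger that cannot operate. File data do not replace the SES, because they are not the primary outcome.

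**Conclusion.** The point holds in this form: the protocol does not fix whether the SES is obtained once care has ended, its expectation of minimal loss rests only on the clinician being the rater, and the sensitivity analysis depends on an unworkable condition. The defect in the trigger needs no assumption about drop-out. The 5.1% margin against cited drop-out from 14% shows that minimal loss is unsupported, not that it is false.

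The main harm is informative missingness. Its possible size, a true 0.40 estimated at about 0.31 to 0.38, is illustrative and requires that every leaver lacks an SES. Power is secondary: about 0.85, 0.80 and 0.72 at 14%, 23% and 37% missing SES, on the plan's effect size and design effect.

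**What to change.** 1. **Statistical analyses:** delete the condition about MAR being violated. State that a pattern-mixture (delta-shift) sensitivity analysis of the SES will always be run, with shifts allowed to differ by arm. The method is already named, so this costs wording and a little analysis time.
2. **Procedures and randomization:** have the last primary clinician complete the SES when treatment ends, alongside the reason already collected, and record agreed completion separately from disengagement. The cost is one 14-item form per leaver. The downside is that ratings then fall at varying times, so timing should be reported by arm. This must be in place before patients leave, because such ratings cannot be recovered reliably later.
3. **Sample size and power calculations:** replace the statement of minimal loss with an assumed range of missing SES and the power at each value, as in the table above.

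A further sensitivity analysis that ranks disengaged patients worst is optional.
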